# 7. Statistical Plan

## Sample Size Determination

This study is powered to detect a difference in microcirculatory function as assessed by iontophoresis. It is likely that if a difference is seen in microcirculatory function as assessed by iontophoresis that the other microcirculatory assessments will follow the same trend

We expect 85% failure in the placebo group and 50% failure in the intervention arm (35% difference in success). We have set alpha=0.05 and beta=0.1 which gives us 90% power.

Therefore:

n=[((15x85)+(50x50))/35^2]x10.5=32 patients in each arm

In order to ensure we achieve a total of 32 patients in each arm for an adequately powered study, we will recruit 40 patients per arm to allow for withdrawals and protocol violations.

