## Primary Study Endpoints

**1. Microcirculatory studies** – pulse wave velocity (PWV), iontophoresis of acetyl choline (AcH) and sodium nitroprusside (SNip), skin autofluoresence (AF) and side stream dark field imaging of the sub lingual microcirculation.

Pulse wave velocity – we expect PWV to decrease after vitamin D therapy.

Iontophoresis – we expect lower skin micro-vessel resistance as measured by laser Doppler Flowmetry (LDF) after vitamin D therapy.

Skin autofluorescence – we expect lower deposition of advanced glycation end products after vitamin D therapy.

Sublingual microvascular flow using sidestream darkfield (SDF) imaging – we expect enhanced flow in patients treated with vitamin D

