## Method for Assigning Subjects to Treatment Groups

Subjects will be randomised to either ergocalciferol or placebo in a 1:1 fashion using a random number generator.

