## Statistical Methods

Full statistical support will be provided for data analysis. Differences between means will be analysed by student’s t test. Multiple regression analyses will be applied to determine which factors are associated with improved microvascular function. STATA software will be used for analysis. Baseline demographics will be recorded for all participants. The study design is in line with CONSORT guidelines.

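### The 90% power is calculated for an undefined binary iontophoresis failure, while the planned analysis is a t test on means whose power cannot be checked

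*Combined protocol and SAP*

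**What the plan says.** Sample Size Determination, in the Statistical Plan, names the endpoint that drives the numbers: "This study is powered to detect a difference in microcirculatory function as assessed by iontophoresis". It then assumes two proportions: "We expect 85% failure in the placebo group and 50% failure in the intervention arm (35% difference in success". The error rates follow: "We have set alpha=0.05 and beta=0.1 which gives us 90% power". The result is "n=[((15x85)+(50x50))/35^2]x10.5=32 patients in each arm", and the section adds that "we will recruit 40 patients per arm to allow for withdrawals and protocol violations". Allocation is 1:1 (Method for Assigning Subjects to Treatment Groups).

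Primary Study Endpoints describes iontophoresis as a measurement: "we expect lower skin micro-vessel resistance as measured by laser Doppler Flowmetry (LDF) after vitamin D therapy". It gives no threshold for success or failure.

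Statistical Methods names one comparison between groups: "Differences between means will be analysed by student’s t test". It adds multiple regression for factors associated with improved microvascular function. Statistical Methodology and Analysis, in the Study Summary, adds a normality check followed by parametric or non-parametric tests. No section names a comparison of proportions, and no section gives a mean difference or an SD for iontophoresis.

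**The concern.** A power statement is useful only if it refers to the quantity and the test that will be reported. Here the calculation refers to a yes/no outcome, while the endpoint and analysis sections refer to a measured response compared by means. A reader of the results could not attach the 90% to the t test.

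The missing definition matters in its own right. The iontophoresis procedure in the Attachments uses two agents, five non-zero current steps and skin preparation on both forearms. The schedule places microcirculatory assessments at five visits, three of them after randomisation. No summary measure, agent or visit is singled out. If a failure cut-off were wanted later, many could be built after the data had been seen. Iontophoresis is also the only endpoint that the main trial is powered on, and the protocol expects the other microcirculatory measures to follow its trend.

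**Working it through.** **Inputs from the protocol.** Failure 85% on placebo and 50% on ergocalciferol, so success 15% and 50%, a difference of 0.35; alpha 0.05; power 90%; 32 evaluable and 40 recruited per arm; 1:1 allocation. Sidedness is not stated, but the multiplier 10.5 matches (1.960 + 1.282)² = 10.51, which is two-sided 5% with 90% power.

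**Step 1: reproduce the protocol's figure.** The formula is the standard unpooled one, n = [p1(1−p1) + p2(1−p2)] / (p1−p2)² × 10.5.

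- (15×85 + 50×50) / 35² × 10.5 = (1275 + 2500) / 1225 × 10.5 = 32.36.
- Rounding up would give 33; the protocol has 32.
- Power at 32 by the same method: 0.35 / √(0.3775/32) − 1.960 = 1.26, which is 89.7%. At 33 it is 90.5%.

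The figure stands as arithmetic. The rounding costs one patient per arm and 0.3 percentage points against the stated 90%.

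**Step 2: sensitivity of the binary figure to the test.** The protocol names no test of proportions, so the rows other than the first show only what would follow if one were chosen. All are for 15% against 50% success, two-sided 5%.

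| Method | 32 per arm | 40 per arm |
| --- | --- | --- |
| Unpooled normal (the protocol's formula) | 89.7% | 95.0% |
| Chi-square, pooled normal approximation | 86.6% | 93.2% |
| Chi-square, exact enumeration | 87.5% | 93.3% |
| Fisher exact, enumeration | 81.5% | 89.8% |

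**Step 3: the planned t test.** No sample size or power can be derived from the protocol, because it gives neither a mean difference nor an SD. What can be derived is the standardised difference detectable with 90% power. A rough check is d = (1.960 + 1.282) / √(n/2), which at n = 32 is 3.242 / 4 = 0.81. The noncentral t distribution gives:

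- 0.82 SD at 32 per arm;
- 0.73 SD at 40 per arm.

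**Step 4: power of the t test over a range of effects.** The first three effects are assumptions, because the documents give none. The last assumes that failure is a cut on a normal variable with equal SD in both arms, so that the implied shift is z(0.85) − z(0.50) = 1.036 − 0 = 1.04 SD.

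| Difference | Power at 32 per arm | Power at 40 per arm |
| --- | --- | --- |
| 0.5 SD (assumed) | 50% | 60% |
| 0.65 SD (assumed) | 73% | 82% |
| 0.8 SD (assumed) | 88% | 94% |
| 1.04 SD (implied by 85% against 50%) | 98% | over 99% |

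Depending on the true difference, the planned test could have far more or far less than the stated 90%.

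**The case against.** The best defence is that the calculation is sound on its own terms and the trial is not small for the effect it expects. The formula is a standard one and gives the stated number apart from rounding. Recruitment is 40 per arm, and When and How to Withdraw Subjects provides for most withdrawn patients to be replaced, with confirmed drug toxicity the exception. If the proportions come from a cut on a normal variable, a t test on the underlying measurement has about 98% power at 32 per arm, since it uses more of the information.

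All of that stands, and it rules out two stronger readings. A reader might infer that even the binary calculation fails, because chi-square and Fisher tests give less than 90% at 32 per arm. The documents do not support this: they name no test of proportions, and the method they do use returns 89.7%. The lower figures show sensitivity to the choice of test, and at 40 per arm they rise to 93% and 90%. A reader might also infer that the planned t test is underpowered. That does not follow either, because its power depends on an effect size that the protocol does not state.

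The defence leaves the mismatch itself untouched. The 98% rests on a definition of failure that the reader has to supply, and on a shift of about one SD that the protocol does not claim for any measured quantity.

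**Conclusion.** The sample size does not match the analysis. This is an inconsistency between sections, not an arithmetic error. The 90% power belongs to an undefined binary outcome that no planned analysis uses, and the power of the planned t test (or its non-parametric substitute) cannot be verified.

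In size: 90% power for the t test means a difference of 0.82 SD with 32 per arm analysed, or 0.73 SD with 40. A null result could not be read as having had 90% power against moderate effects; at an assumed 0.5 SD the power is 50% to 60%. These figures assume a two-sided 5% test, equal SDs and approximate normality. The 1.04 SD shift also assumes that failure is a cut on a normal variable.

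The point concerns the main trial only. Appendix 1 describes the additional arm as a pilot without a reliable power calculation. The correction should be made before unblinding, because the endpoint on which the trial is powered is otherwise open to definition afterwards.

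**What to change.** Preferred: name one continuous iontophoresis variable as the powered endpoint before unblinding, stating the agent, the dose-response summary and the visit. Replace the binary calculation with a statement such as: *32 evaluable (40 randomised) patients per arm give 90% power to detect a difference of 0.82 SD (0.73 SD) with a two-sided 5% t test.* Convert this to laser Doppler units with the between-patient SD from the assessments at visits 2 and 3, provided that the visit 3 assessment precedes the first capsule. Then say whether a difference of that size is plausible and would matter.

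Alternative: if a responder outcome is meant, define its cut-off now, make a named test of proportions the primary analysis, and restate the power for that test: about 87% by chi-square or 82% by Fisher at 32 per arm.

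Neither option needs more patients or visits. The real cost is commitment: the protocol currently sets no iontophoresis summary measure and no primary time point, so this is a new decision as well as a change of wording. The stated power becomes less favourable only under the binary option.

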## Statistical Methods

Full statistical support will be provided for data analysis. Differences between means will be analysed by student’s t test. Multiple regression analyses will be applied to determine which factors are associated with improved microvascular function. STATA software will be used for analysis. Baseline demographics will be recorded for all participants. The study design is in line with CONSORT guidelines.

## Subject Population(s) for Analysis

We will recruit patients from the Royal London Hospital general nephrology outpatient clinics who match inclusion criteria as specified previously. Up to 40 patients in each arm will be recruited (80 in total). Patients will be provided with a full explanation of the purpose and details of the study and will receive a patient information sheet. Written informed consent will be obtained. Patients will undergo a screening evaluation to determine if they meet the study inclusion and exclusion criteria. This will include a medical history and physical examination as well as a review of all relevant existing blood tests.

Healthy volunteers will be recruited by advertisement to staff and students of Queen Mary, University of London and The Barts & the London NHS Trust and to the general community, as approved by a National Research Ethics Service (NRES) approved Research Ethics Committee.

## Informed consent procedures

### It is the responsibility of the Investigator, or a person delegated by the Investigator (the delegation log needs to spell out who is authorised to take consent, only GCP trained individual can take consent) to obtain written informed consent from each subject prior to participation in this study, following adequate explanation of the aims, methods, anticipated benefits and potential hazards of the study.

### Ample time must be given for consideration by the patient before taking part. The PI must record when the patient information leaflet (PIL) has been given to the patient. [If the amount of time between the PIL being given and the date of consent is less than 24 hours, the PI needs to explain why this is the case in this study].

### The Investigator or designee must explain the subjects are completely free to refuse to enter the study or to withdraw at any time during the study, for any reason.

### If new safety information results in significant changes in the risk/benefit assessment, the consent form should be reviewed and updated if necessary. All subjects, including those already being treated, should be informed of the new information, giving a copy of the revised form and give their consent to continue in the study.

# Safety and Adverse Events

## Expected Adverse Events

1. Hypercalcaemia

2. Starting any form of renal replacement therapy (haemodialysis, peritoneal dialysis, kidney transplant)

3. Mild skin erythema over the site of the iontophoresis ion chambers

4. Undergoing surgery for dialysis access

5. Hospital admission due to sepsis

6. Admission to hospital due to poorly controlled blood pressure

7. Hospital admission for any form of cardiovascular event eg stroke, myocardial infarction etc.

7. Claustrophobia in MRI scanner

8. Mild skin reaction to ECG labels

9. Any elective admission to hospital which is unrelated to the study protocol or admission to hospital as a result of an unrelated medical procedure

10. Allergic reaction or any other medical problems related to contrast media from the cardiac MRI scan.

## Definition of Adverse Events

Adverse Event

An AE is any untoward medical occurrence in a subject to whom a medicinal product has been administered, including occurrences which are not necessarily caused by or related to that product. An AE can therefore be any unfavourable and unintended sign (including an abnormal laboratory finding), symptom or disease temporarily associated with the use of an Investigational Medicinal Product (IMP), whether or not considered related to the IMP. All such events during this trial will be recorded in the CRF.

Adverse Reaction (AR)

An AR is any untoward and unintended response in a subject to an Investigational Medicinal Product (IMP), which is related to any dose administered to that subject. All adverse events judged by either the reporting investigator or the Sponsor as having a reasonable causal relationship to a medicinal product qualify as adverse reactions. The expression reasonable causal relationship means to convey in general that there is evidence or argument to suggest a causal relationship.

Serious Adverse Event (SAE)

An SAE fulfils at least one of the following criteria:

- Is fatal – results in death (NOTE: death is an outcome, not an event)
- Is life-threatening
- Requires inpatient hospitalisation or prolongation of existing hospitalization
- Results in persistent or significant disability/incapacity
- Is a congenital anomaly/birth defect

## The above is a broad definition of an SAE. Hospitalisations for elective

## procedures and certain expected adverse events may be exempt from

## this reporting process, if specified in the trial protocol. Additional

## significant medical events may be classed as SAEs.

Suspected Serious Adverse Reaction (SSAR)

An SSAR is an adverse reaction that is classed as serious and which is consistent with the information about the medicinal product as set out in the Summary of Product Characteristics (SmPC) or Investigator’s Brochure (IB) for that product.

Suspected Unexpected Serious Adverse Reaction (SUSAR)

The definition of a SUSAR is any suspected unexpected adverse reaction related to an IMP that is both unexpected and serious. In this case the event is not outlined in the Summary of Product Characteristics (SmPC) or Investigator’s Brochure (IB) for that product.

Critical Adverse Events

A critical adverse event is an event which may not be classified as serious but is considered to be important to the evaluation of safety. These events may become apparent as the trial progresses and requires close communication between the sponsor and investigators.

## Recording of Adverse Events

All events will be recorded on the Adverse Event forms in the patient’s record and a copy will be kept in the CRF.

## Notification and Reporting of Serious Adverse Events/SUSAR

**For UK MAI IMP licensed IMPs only:** As the IMP’s used in this project are licensed in the UK and used within their marketing authorization, the EXPECTED SARs (outlined in the SmPCs) will be RECORDED in the subjects notes and in the CRF. No SAE forms will be completed and sent to the sponsor.

UNEXPECTED Serious Adverse Event (SAE’s) will be recorded in the subjects notes, the CRF and in the sponsor SAE form and reported to the JRO within one working day of the PI or co-investigators becoming aware of the event. The co-investigators listed in this protocol will be authorized to sign the SAE forms in the absence of the PI. Suspected Unexpected Serious Adverse Reactions (SUSAR’s) during the trial will be reported to the JRO and the main REC within one working day of the PI or co-investigator becoming aware of the event.

## When Adverse Events are Recorded

Events will be recorded at each patient visit. Patient’s will asked specifically if any expected adverse events have occurred or if any other events have occurred in the interval between the last patient visit. Non-leading questions such “How do you feel?” and “have you had any problems since I last saw you?” will be asked at each visit.

## Study Stopping Rules

Subjects who are withdrawn because of serious adverse events (including a Grade 3 or 4 toxicity (based on the Common Toxicity Criteria (CTC) version 3.0 – included with this document) will not be replaced. The Ethics Committee will be notified in writing of any study withdrawals that may occur as a result of toxicity.

The study will be stopped if there are any major safety concerns involving the patients involved in the trial as raised by the sponsor or the principal investigator. The study will end when the last patient has received the last dose of study medication and undergone the final assessments as in section 7.

## Unblinding Procedures

Patients and investigators will be unblinded if they are admitted to hospital with hypercalcaemia. Unblinding will be required as there are a number of common medical conditions (myeloma, tuberculosis, sarcoidosis etc) that can cause hypercalcaemia and should be ruled out urgently if a study patient who is taking placebo rather than ergocalciferol presents with symptoms/signs of hypercalcaemia.

Mawdsley Brooks UK will hold a master randomisation list which will be able to identify which arm any subject is in. There is a 24 hour trial hotline which can be contacted by clinical staff at any time should unblinding be required for medical reasons. Furthermore, individual code break envelopes will be available to clinicians at the Royal London Hospital. All renal staff will have access to code break procedures and envelopes which will be locked in a secure office with an entry code on the door.

Code-breaks should only occur when absolutely necessary and beneficial to the patient. In the event of a code break, the sponsor and PI will be informed.

## Medical Monitoring

Patients will be reviewed at each visit by an investigator. They will undergo routine evaluations for standard outpatient care as well as more detailed evaluations as required by the trial protocol. This will include a medical history, examination, blood tests for the trial and others as necessary based on clinical evaluation.

**8.10** The Annual Safety reports (ASR) will be sent by the PI to the sponsor and MHRA (the date of the anniversary is the date on the “notice of acceptance letter” from the MHRA) using the sponsor ASR form. The PI will carry out a risk benefit analysis of the IMPs encompassing all events having arisen on the trial.

**8.11** The Annual progress report will be sent to the main REC (the anniversary date is the date on the MREC “favourable opinion” letter from the MREC) and to the sponsor.

# Data Handling and Record Keeping

## Confidentiality

All computers used will be kept on NHS property and password protected. Each patient’s information will be recorded against an individual code which will be stored on a NHS password protected computer. CRF’s will not contain names, rather the study code for that participant and their initials. Every effort will be made to respect patient confidentiality throughout the trial duration.

## Study Documents

All relevant documents and correspondence will be kept in the patient’s records. Computerised trial documents will be password protected and held on NHS computers at the Royal London Hospital. The investigator and sponsor will have access to these records.

## Case Report Forms

The case report from will contain details of the study name, protocol number, subject initials and trial ID code and other relevant information. It will have a check list for the inclusion and exclusion criteria. It will also contain reporting forms for AE’s, SAE’s and SUSAR’s.

CRF’s for all patients, including those excluded from the study for any reason, will be kept and maintained by the PI. CRF forms are to be completed in black pen and in their entirety with no blank spaces allowed unless data is not available or applicable. This fact must be indicated. Corrections must be struck-through and the correct information entered adjacent to this and initialled and dated by the investigator. Completed CRF’s are to be returned to the sponsor as soon as is practical. Copies are to be retained by the Principal investigator.

## Records Retention

All records will be held in the archive system for 20 years following the start of the trial.

# Study Monitoring, Auditing, and Inspecting

## Study Monitoring Plan

The principal and chief investigator will meet after three months to review AE’s, SAE’s and SUSAR’s. The trial may be subject to routine auditing by Research Governance at Barts and the London NHS Trust.

**Phase IV trials:**

It is the CI’s responsibility to ensure that the BLT monitoring template (designed especially for the BLT/QM sponsored CTIMPs) is completed in a CONTINUOUS fashion throughout the study and kept up to date by the co-investigators (for the first part of the report) and by the MONITORS NAMED ON THE FIRST PAGE OF THIS PROTOCOL (for both the first part and the source data verification part of the template.). This trial is a Phase IV trial, using IMPs licensed in the UK and used within their marketing authorisation, this project is therefore risked as a “low risk (risk B)” project and the monitoring report will be sent to the JRO a year after the first consent has been signed and annually there after.

# Ethical Considerations

General considerations:

The study will be conducted in accordance with the principles of the Declaration of Helsinki (1997) (Recommendations guiding Medical Doctors in Biomedical Research Involving Human Subjects).

Every effort will be made to minimize discomfort and disruption to the trial participants.

All relevant study documentation will be submitted to a National Research Ethics Service (NRES) and no trial activity will begin until approval from this body has been received. A copy of ethical approval will be forwarded to the sponsor. If ethical approval is suspended or terminated, the sponsor will be informed immediately. Trial progress will be reported to the ethics committee once a year. All SAE’s will be reported to the ethics committee as soon as possible and at least within 72 hours.

Study specific ethical considerations:

1. The endpoints of this trial (both in vivo and in vitro) have never been addressed in the setting of a randomized clinical trial. New and relevant information which will change practice to enhance patient care and could influence CKD guidelines can be generated by undertaking this study.

2. The study drug, ergocalciferol, is in routine use for vitamin D deficiency in a number of clinical settings. It has a low side effect profile and is considered to be safe and efficacious.

3. Placebo controlled trials have been in routine use in medical research for years. If a benefit is shown in the ergocalciferol arm, patients who have received placebo can be eligible for ergocalciferol treatment when the trial ends.

4. Secondary hyperparathyroidism (SHPT) is a recognized consequence of CKD and is treated by vitamin D therapy. It is possible that patients with modestly elevated PTH levels will receive placebo tablets. This means that their SHPT will go untreated for 6 months. However, an analysis of PTH levels in an existing group of patients at the Royal London Hospital with CKD and vitamin D deficiency has shown a low median PTH value (median 11.7, standard deviation 19.44 pmol/L). This level of PTH is unlikely to have any serious clinical consequences if not treated over the trial duration and we do not believe patients are at risk by potentially not receiving ergocalciferol. Patients will be reassured about the safety of the drug and the safety and validity of undertaking a randomized, placebo controlled trial.

5. Patients will be required to attend more frequently than normal and have more blood tests (with the associated discomfort) than they might expect in their routine care. Other tests will be required which patients may not have had. A full explanation and support will be offered to patients at every stage of the trial. We will undertake as many trial procedures in a single visit as possible to minimize disruption to the patients.

6. Blood and urine samples will be stored for further analysis relating to the trial. Patients will be clearly informed of this.

